**Mortality at 30 days**

Information about patients’ status will be sought in those who are discharged before 30 days on Day 30 from randomisation.

Time to the occurrence of each of these events will be recorded.

Each of these events will be analysed as a binary outcome and as a time-to-event one.

**2.4.3 Primary safety endpoint:**

Major bleeding, defined as an acute clinically overt bleeding associated with one or more of the following:

- Decrease in haemoglobin of 2 g/dl or more;
- Transfusion of 2 or more units of packed red blood cells;
- Bleeding that occurs in at least one of the following critical sites [intracranial, intraspinal, intraocular (within the corpus of the eye; thus, a conjunctival bleed is not an intraocular bleed), pericardial, intra-articular, intramuscular with compartment syndrome, or retroperitoneal];
- Bleeding that is fatal (defined as a bleeding event that was the primary cause of death or contributed directly to death);
- Bleeding that necessitates surgical intervention

Time to the occurrence of each of these events will be recorded.

Each of these events will be analysed as a binary outcome and as a time-to-event one.

- - 1. **Secondary safety endpoint:**

Clinically Relevant non-major bleeding, defined as an acute clinically overt bleeding that does not meet the criteria for major and consists of:

1. Any bleeding compromising hemodynamics
2. Spontaneous hematoma larger than 25 cm^2^, or 100 cm^2^ if there was a traumatic cause
3. Intramuscular hematoma documented by ultrasonography
4. Epistaxis or gingival bleeding requiring tamponade or other medical intervention
5. Bleeding from venipuncture for >5 minutes
6. Hematuria that was macroscopic and was spontaneous or lasted for more than 24 hours after invasive procedures
7. Hemoptysis, hematemesis or spontaneous rectal bleeding requiring endoscopy or other medical intervention
8. Any other bleeding requiring temporary cessation of a study drug.

Time to the occurrence of each of these events will be recorded.

Each of these events will be analysed as a binary outcome and as a time-to-event one.

**2.4.4 Risk/benefit Ratio**

Recently published data have shown that the use of low-dose heparin in patients admitted to hospital with COVID-19 and severe pneumonia and coagulopathy, reduces mortality from about 60% to about 30%.

We assume that higher doses of LMWH in these patients might be more effective than low doses in reducing the risk of clinical worsening. At the same time, we are aware that the administration of high doses of LMWH might be associated with a higher risk of bleeding. However, we think that the possible increased risk of major bleeding could be negligible, as Wein et al [16] reported a risk of major bleeding between 1.4% and 2.29% with low doses of LMWH, whereas Pengo et al [17] reported a 2.7% risk when LMWH was given at high doses.

We think that on these premises, the risk/benefit of the intervention is favourable for severe COVID-19 patients and allows us to consider the study worth carrying out.

**2.4.3 Physiological and Processes of care outcomes**

- Vital signs such as systolic and diastolic arterial pressure, heart rate (HR), respiratory rate (RR) and systemic body temperature will be recorded daily from inclusion until hospital discharge (censored day 28);
- Routine laboratory test parameters for organ function assessment: blood cells count, coagulative parameters (INR, PT, aPTT, fibrinogen, D-dimer), parameters for liver (AST, ALT, bilirubin) and renal function (creatinine) and interleukin 6 (IL-6) will be recorded at least at the moment of randomization, after 48 and 96 hours, then according to clinical judgement of the attending physician until hospital discharge.

**2.5 PARTICIPANT TIMELINE**

See APPENDIX 2 for a timeline-scheme of the trial.

**2.6 SAMPLE SIZE**

The target sample size is based on the hypothesis that LMWH administered at high doses versus low doses will significantly reduce the risk of clinical worsening. The overall sample size in this study is expected to be 300 with a 1:1 randomisation ratio. Assuming an alpha of 5% (two tailed) and a percentage of patients who experience clinical worsening in the control group being between 25% and 30%, the study will have 80% power to detect at least 50% relative reduction in the risk of death between low and high doses of heparin.

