| **Statistical Considerations**  **& Sample Size** | **Statistical Considerations**  The efficacy will be assessed by estimating the difference between the two treatment arms in the proportion of participants experiencing clinical worsening during their hospital stay.  Safety will be assessed by estimating the difference between the two treatment arms in the proportion of participants who experience at least one bleeding event (major or non-major) during their hospital stay.  Relative risk (RR) will be used as measure of association, which will be reported with its 95% confidence interval.  The differences between the two arms in the variation of:   1. D-dimer level 2. Plasma fibrinogen levels   3) Mean platelet Volume  4) Lymphocyte/Neutrophil ratio  5) IL-6 plasma levels  at 3 time points (at randomization, at 48 hours and 96 hours) will be assessed.  These outcomes will be compared by using their mean values and summary indicators.  Overall survival, survival free from any cardiovascular event, such as Acute Myocardial Infarction [AMI], Objectively confirmed, symptomatic arterial or venous thromboembolism [TE] and survival free from need for either non-invasive or invasive mechanical ventilation will be also estimated. They will be reported by using Kaplan-Maier curves and compared by using hazard ratio (HR).  **Sample size**  300 participants will be needed to detect a relative reduction of 50% of clinical worsening. We hypothesized that the percentage of participants who experience clinical worsening in the LMWH low dose group would be around 25-30% and set an alpha error of 0.05 and beta-error of 0.20. | |
| **Treatment Schedule** | **Control group (Low Dose):** Enoxaparin (Inhixa®) 4000 IU subcutaneously once daily.  **Intervention group (High dose**): Enoxaparin (Inhixa®) 70 IU/kg subcutaneously twice daily.  Participants will receive the dose of Enoxaparin according to the protocol until the occurrence of at least one of the following events:   1. One of the events included in the primary outcome 2. Hospital discharge 3. Any adverse events and clinical condition requiring interruption of the scheduled intervention according to the judgement of the physician in charge | |

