**1.1.3 Benefits of the use LMWH**

As reported in the previous section, the use of LMWH or Unfractionated Heparin (UFH) at prophylactic doses has been shown to be associated with a reduced mortality at 28 days in COVID-19 patients with severe pneumonia and Sepsis Induced Coagulopathy (SIC) score ≥4 (40.0% vs 64.2%, P=0.029), or D-dimer > 6-fold of upper limit of normal (32.8% vs 52.4%, P=0.017 [11]. This finding is consistent with the well-known immune-modulatory properties and protective action of glycocalyx from shedding displayed by heparin. [15].

However, no evidence is available about the clinical question of whether higher doses of LMWH improve the prognosis of more severe COVID-19 patients.

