**4.4 Analyses ad interim**

Considering the statistical approach, an interim analysis is planned after the randomisation of 150 patients (50% of sample size) for the double objective of monitoring safety and verifying the accuracy of the assumptions made for sample size estimation, regarding the event rate of the primary outcome in relation to the anticipated survival benefit. With the interim analysis we will be able to evaluate whether the data suggests that there is substantial superiority of one treatment. The obtained results will be evaluated by the DSMB and by the SC and, in case of significant differences in survival among the groups, all patients will be switched to the most promising treatment.

1. **SAFETY CRITERIA EVALUATION**
   1. **Safety profile**

Data on safety profile, nature, incidence and severity of adverse events (AEs) and serious adverse events (SAEs) will be collected. Any reason for drug interruption, reduction and discontinuation will be collected. Toxicities will be graded using NCI Common Terminology Criteria for adverse Events (CTCAE) version 4.03.

- 1. **Adverse events (AE) and serious adverse events (SAE)**

The investigator is responsible for the detection and documentation of AE and SAE events, according to the criteria defined in this protocol. During the safety evaluation, the Investigator or site staff will be responsible for detecting, documenting and reporting AEs and SAEs, as detailed in both this section of the protocol and in the AE/SAE section of the CRF.

- - 1. **Definition of an AE**

An AE is defined as any untoward medical occurrence in a patient, temporarily associated with the use of a medicinal product, whether or not it is considered related to the medicinal product. An AE can therefore be any unfavourable and unintended sign (including an abnormal laboratory finding), symptom, or disease (new or exacerbated) temporarily associated with the use of a medicinal product. For marketed medicinal products, this also includes failure to produce expected benefits (i.e. lack of efficacy), abuse or misuse.

Examples of an AE include:

- Significant or unexpected worsening or exacerbation of the condition/indication under study.
- Exacerbation of a chronic or intermittent pre-existing condition including either an increase in frequency and/or intensity of the condition.

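### Section 2.6 attaches its 80% power to death, although its hypothesis and control rate are for clinical worsening; the mortality figures in 2.4.4 and 1.1.3 also need reconciling

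*Protocol*

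**What the plan says.** Section 2.6 opens with the hypothesis that high-dose heparin reduces clinical worsening. It sets 300 patients at 1:1, a two-tailed alpha of 5%, and "a percentage of patients who experience clinical worsening in the control group being between 25% and 30" per cent. The same sentence ends with "80% power to detect at least 50% relative reduction in the risk of death".

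The synopsis gives the same total and the same control rate for the composite: "300 participants will be needed to detect a relative reduction of 50% of clinical worsening". It adds that the investigators "set an alpha error of 0.05 and beta-error of 0.20". Section 2.4.1 defines the primary efficacy endpoint as clinical worsening, with death as one of five components. Death during the hospital stay and mortality at 30 days are secondary endpoints in 2.4.2.

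Section 4.4 says the interim analysis will check the sample-size assumptions "regarding the event rate of the primary outcome in relation to the anticipated survival benefit". It then ties action to significant differences in survival.

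Two other sections quote mortality. Section 2.4.4 says low-dose heparin "reduces mortality from about 60% to about 30" per cent in hospitalised patients with severe pneumonia and coagulopathy. Section 1.1.3 reports 28-day mortality with and without heparin in two subgroups, defined by SIC score and by D-dimer: "40.0% vs 64.2%, P=0.029), or D-dimer > 6-fold of upper limit of normal (32.8% vs 52.4" per cent.

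**The concern.** A power statement joins an endpoint, a control rate for that endpoint and an effect. Section 2.6 takes its rate from the composite and its effect from one component. As written, it tells the ethics committee and the data safety monitoring board that the trial has 80% power for mortality. Nothing in the section supports that.

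The same slip may carry into the interim analysis. Section 4.4 sets the event rate of the primary outcome against a survival benefit, but the sample size was not derived from survival.

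The background figures do not settle which rate applies. The halving in 2.4.4 is larger than either reduction in 1.1.3. It also puts mortality on the control regimen at about the level assumed for the whole composite. If that mortality applied to this trial, the 25-30% rate would leave almost no room for ventilation, infarction or thromboembolism in surviving patients.

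**Working it through.** **Inputs.** 150 per arm, two-sided alpha 0.05 and control rate 25-30% (section 2.6); power 80% (2.6 and synopsis); 50% relative reduction (2.6 and synopsis). The documents give no planned control death rate. The 10%, 15% and 20% used below are assumptions, chosen to show a range below the composite rate.

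**Formulas.** With p1 the control rate, p2 = p1/2, p̄ their mean, d = p1 − p2, and n per arm:

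- A = 1.96 × √[2p̄(1−p̄)/n]
- B = √{[p1(1−p1) + p2(1−p2)]/n}
- power = Φ[(d − A)/B]

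**1. The plan's own figure, for clinical worsening.** For 25% to 12.5%, the pooled formula for sample size gives

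n = [1.96√0.3047 + 0.8416√0.2969]² / 0.125² = 151.9,

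which is 152 per arm or 304 in total. The unpooled version gives 7.849 × 0.2969/0.015625 = 149.1, which is 150 per arm or exactly 300. For 30% to 15%, the pooled formula gives 121 per arm or 242 in total. The stated 300 is therefore reproduced at the 25% end and is more than enough at 30%.

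**2. Power with 150 per arm for a halving.**

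| Endpoint | Control → treated | d | A | B | (d−A)/B | Power |
|---|---|---|---|---|---|---|
| Clinical worsening | 25% → 12.5% | 0.125 | 0.0883 | 0.0445 | 0.824 | 79.5% |
| Clinical worsening | 30% → 15% | 0.150 | 0.0945 | 0.0474 | 1.170 | 87.9% |
| Death (assumed) | 10% → 5% | 0.050 | 0.0596 | 0.0303 | −0.317 | about 38% |
| Death (assumed) | 15% → 7.5% | 0.075 | 0.0715 | 0.0362 | 0.096 | about 54% |
| Death (assumed) | 20% → 10% | 0.100 | 0.0808 | 0.0408 | 0.470 | about 68% |

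A component cannot be more frequent than the composite that contains it. Under the premise of 2.6, control mortality is therefore at most 25-30%. Power for death reaches about 80% only if death alone is about 25%, that is, nearly all of the composite.

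**3. The mortality figures.**

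- Section 1.1.3, SIC subgroup: (64.2 − 40.0)/64.2 = 37.7% relative, 24.2 points absolute.
- Section 1.1.3, D-dimer subgroup: (52.4 − 32.8)/52.4 = 37.4% relative, 19.6 points absolute.
- Section 2.4.4: (60 − 30)/60 = 50% relative, 30 points absolute.

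Neither pair in 1.1.3 is a halving. The treated rates (about 30%, 32.8% and 40.0%) all lie at or above the top of the 25-30% assumed for the composite.

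**The case against.** The strongest reply is that the arithmetic is right and only one word is wrong. Section 2.6 itself opens with clinical worsening, and the synopsis and 2.4.1 agree. The sample size, alpha, primary endpoint and analysis do not change. That stands, and it rules out one tempting reading: that the stated power is not delivered and the trial is too small. For the primary endpoint it is delivered, to within half a point at 25%. Only a continuity-corrected or exact test would fall to about 75% there, and the protocol specifies neither.

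Nor is a shortfall for death proven. It needs control mortality below about 25%. At the mortality the protocol quotes elsewhere, power to halve death would be 87.9% (at 30%), 91.4% (32.8%) and 96.9% (40.0%). But those rates do not rescue 2.6, because in the same population they would contradict its own 25-30% composite rate. The two premises cannot be used together, and the sponsor has to say which applies.

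A reader might also infer that a 25-30% composite rate is impossible. The documents do not go that far. The rates in 1.1.3 come from subgroups with SIC score of 4 or more or D-dimer above 6-fold. The trial admits D-dimer above 4 times normal and excludes, among others, invasively ventilated patients, those over 80 and those with limited life expectancy. Lower rates are possible. Still, 2.4.4 applies its 30% to a population described much like the trial's, so the rate needs a justification.

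Two more inferences go too far. One is that 2.4.4 joined the untreated rate of one subgroup to the treated rate of the other; that section cites only recent data, so this is a guess. The other is that the 50% hypothesis was taken from that halving and power should be restated at 37-38%. Nothing in 2.6 or the synopsis derives the effect that way, and the 1.1.3 data compare heparin with none on mortality, not high with low dose on a composite.

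Finally, the synopsis speaks of survival free from various events, so the survival wording in 4.4 may be loose rather than a change of endpoint. That is a reason to clarify it, because action at the interim depends on it.

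**Conclusion.** The point holds as an error in the stated endpoint, plus unreconciled background rates. Section 2.6 assigns 80% power to death using inputs that belong to clinical worsening, in conflict with the synopsis and with its own first sentence. For clinical worsening, 300 patients give 79.5% to 87.9% power across the assumed control range.

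For death the 80% is unsupported. The size of any shortfall depends on a control mortality that the protocol does not plan for; the values of about 38% to 68% rest on the assumed 10-20% and illustrate the direction only.

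The conflict between 2.4.4 and 1.1.3 is certain on the figures printed. The tension between quoted mortality of 30-40% and a 25-30% composite shows an assumption that needs justifying, not one proven wrong. The 2.6 wording should be corrected, since a power claim in a sample-size section is read as a commitment and the correction is cheap.

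**What to change.** - **Section 2.6:** name clinical worsening instead of death as the endpoint of the power statement. Claim no 80% power for mortality, which is a secondary endpoint. Do not enter the assumed 10-20% mortality as if it were a planning figure.
- **Section 4.4:** refer the check of the sample-size assumptions to clinical worsening instead of a survival benefit. Reconcile the later wording on differences in survival with the primary outcome.
- **Section 2.4.4:** bring the mortality figures into line with 1.1.3 (64.2% to 40.0% and 52.4% to 32.8%), or cite the separate source if there is one.
- **Section 2.6 and synopsis:** justify the 25-30% composite rate against the quoted low-dose mortality, for example by stating how the trial population differs from the cited subgroups.

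The cost is wording only. The sample size, alpha and primary analysis stay as they are; what is lost is the power claim for mortality.

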**2.7 RECRUITMENT**

All centres participating in this study are experienced in investigator-initiated studies. On the basis of a conservative estimate, each of the 10 participating sites is expected to see around 4 eligible patients per month (40 patients/month). Assuming that 80% of those patients will be enrolled, the recruitment of 300 participants will be completed in around 10-11 months. This period could be shorter if other centres join the study.
Every month, recruitment status will be evaluated, and a newsletter will be disseminated, including any practical, clinical or scientific issues that have arisen.

**3.0 METHODS: ASSIGNEMENT OF INTERVENTIONS**

**3.1 Allocation and blinding**

Randomisation will be centrally performed by using a secure, web-based system, which will be developed by the Methodological and Statistical Unit at the Azienda Ospedaliero-Universitaria of Modena. Randomisation stratified by 4 factors: 1) Gender (M/F); 2) Age (<75/≥75 years); 3) BMI (<30/≥30); 4) Co-morbidities (0-1/>2) with random variable block sizes will be generated by STATA software. The web-based system will guarantee the allocation concealment. The physicians involved in the study, once they have obtained the patient’s consent, will connect to the website and will register the patient that meets inclusion criteria. The system will also allow the randomisation of the patient and the arm to which he/she is allocated will appear on the monitor. The physician who performed the randomisation will communicate which dose the patient will receive to the colleagues who are in charge of administering LMWH. The information collected during the patient follow-up will be entered on the website and stored on the Hospital’s server. The local coordinator will be in charge of training the personnel involved in the study according to what is stated in the protocol. The study is conceived as open label, i.e. the patients and all healthcare personnel will be aware of the group allocation.

**4.0 METHODS: DATA COLLECTION, MANAGEMENT, ANALYSIS AND MONITORING**

**4.1 Data collection and management**

Every patient who meets the inclusion criteria will be included and randomised in the two groups. The study data will be collected during the entire study period in a dedicated electronic Case Report Form (eCRF).

The eCRF will be provided by the Steering Committee (SC) with proper options to minimize data entry errors: the datasheet will incorporate un-amendable fixed intervals of values (for continuous variables) and pre-defined coding system (for binary or categorical variables). Data entry will be performed and double-checked by a dedicated team of researchers. Data will be collected and stored on the hospital server, which will be protected by password to prevent unintentional modification or deletion. Data related to the study will be stored for eventual further analysis or study purpose for 10 years after the end of the study.

All the data about the included patients will be recorded in an eCRF by trained researchers.

Demographic information, symptoms and co-morbidities, will be registered at the inclusion. During the study duration, the following clinical and laboratory parameters will be evaluated and recorded according to the timeline schedule reported in APPENDIX 2:

- Vital signs such as systolic and diastolic arterial pressure, heart rate (HR), respiratory rate (RR) and systemic body temperature will be recorded daily from inclusion until hospital discharge;

- Routine laboratory test parameters for organ function assessment: blood cells count, coagulative parameters (INR, PT, aPTT, fibrinogen, D-dimer), parameters for liver (AST, ALT, bilirubin) and renal function (creatinine) and interleukin 6 (IL-6) will be recorded at least at the moment of randomisation, after 48 and 96 hours, then according to clinical judgement of the attending physician until hospital discharge.

**4.2 Statistical Methods**

All patients enrolled in the study will be entered in the full analysis set independently of his/her treatment time. The intention to treat population will be considered for primary analysis. A descriptive statistical analysis will be carried out to summarise every relevant variable. At baseline, categorical data will be summarised by using counts and percentages, whilst continuous variables will be presented using the number of patients, mean, standard deviation, median, minimum, and maximum. Comparison between binary outcomes will be performed by using Relative Risks (RRs), whereas for continuous data, the difference of means (DMs) will be used. Comparisons involving time to event data will be displayed by using Kaplan-Maier survival curves and summarised by Hazard Ratios (HRs).

All measures of association will be presented with their 95% confidence interval. A result will be considered as statistically significant if its p-values will be less than 0.05 (5%).

The analyses will be performed by using STATA software.

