**2.4 OUTCOMES**

**2.4.1 Primary Efficacy Endpoint:**

Clinical worsening, defined as the occurrence of at least one of the following events, whichever comes first:

1. Death
2. Acute Myocardial Infarction [AMI]
3. Objectively confirmed, symptomatic arterial or venous thromboembolism [TE]
4. Need for either non-invasive - Continuous Positive Airway Pressure (Cpap) or Non-Invasive Ventilation (NIV) - or invasive mechanical ventilation for patients, who are in standard oxygen therapy by delivery interfaces at randomisation
5. Need for invasive mechanical ventilation for patients, who are in non-invasive mechanical ventilation at randomisation

Time to the occurrence of each of these events will be recorded.

Clinical worsening will be analysed as a binary outcome as well as a time-to-event one.

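### Section 3.1: the co-morbidity strata have no place for a patient with exactly two co-morbidities; naming the covariates in section 4.2 is a secondary, low-cost improvement

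*Protocol*

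**What the plan says.** Protocol section 3.1 sets the allocation rule: "Randomisation stratified by 4 factors: 1) Gender (M/F); 2) Age (<75/≥75 years); 3) BMI (<30/≥30); 4) Co-morbidities (0-1/>2". Randomisation is central and web-based, with random variable block sizes, and the system is still to be developed.

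Section 4.2 names the effect measures. For binary outcomes it says "Comparison between binary outcomes will be performed by using Relative Risks (RRs"; for continuous outcomes it names a difference of means and for time-to-event outcomes a hazard ratio, all with 95% confidence intervals. It mentions no covariate and no stratification term, and it does not call the analyses crude or unadjusted.

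Section 2.4.1 makes the ventilation component of the primary endpoint depend on support at randomisation. On standard oxygen, either non-invasive or invasive ventilation counts. For the others the component is "Need for invasive mechanical ventilation for patients, who are in non-invasive mechanical ventilation at randomisation". That baseline status is not among the four stratification factors.

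**The concern.** A stratified allocation list needs levels that are mutually exclusive and exhaustive. Sex, age and BMI meet this; the co-morbidity levels do not. A system programmed literally could not place a patient with two co-morbidities. If the gap is closed informally, the same kind of patient might be coded differently from one case to the next. The balance that the factor is meant to give would weaken, and the variable would be ambiguous as a later covariate.

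The secondary matter is precision. If the stratification factors are prognostic, an analysis that leaves them out has standard errors that are slightly too wide. Respiratory support at randomisation determines which event a patient can have, yet balance on it is left to chance, and section 4.2 does not say whether it enters the model.

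**Working it through.** **1. Are the levels exhaustive?**

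| Factor in 3.1 | Levels | Values left out |
| --- | --- | --- |
| Sex | male / female | none |
| Age | below 75 / 75 and over | none |
| BMI | below 30 / 30 and over | none |
| Co-morbidities | 0 to 1 / more than 2 | exactly 2 |

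The at-least sign is printed correctly for age and BMI in the same sentence, so loss of the symbol in text extraction is unlikely. Four binary factors give 2^4 = 16 strata. Patients with two co-morbidities fall outside all of them, in each of the 2^3 = 8 combinations of sex, age and BMI. The protocol gives no distribution of co-morbidity counts, so the number affected is unknown; for every 10% of patients with exactly two, it is 0.10 × 300 = 30.

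**2. The plan's own sample size.** Inputs from section 2.6: "Assuming an alpha of 5% (two tailed"), 80% power, a 50% relative reduction (read as applying to clinical worsening, as in the synopsis), control rate 25% to 30%, 150 per arm. At 25% vs 12.5%:

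- Unpooled variance: n per arm = (1.960 + 0.842)² × (0.25×0.75 + 0.125×0.875) / 0.125² = 7.849 × 0.296875 / 0.015625 = 149.1, so 150 per arm and 300 in total.
- Pooled variance: 152 per arm, 304 in total. Power with 150 per arm is 79.5%.

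The stated 300 is reproduced with a plain two-proportion comparison, and nothing in this point changes it.

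**3. What would a crude analysis cost?** The protocol gives no prognostic strengths, so these are simulations under assumptions: 300 patients, blocks of 4 and 6 in 16 strata, control risk 27.5%, 30% on non-invasive ventilation at baseline. Assumed odds ratios for the four factors and for baseline ventilation: weak 1.2–1.3 and 1.5; moderate 1.5–2 and 2.5; strong 2–3 and 4. MH is the Mantel-Haenszel RR, over the 16 strata or over 32 cells with ventilation status added.

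| Strength | Type I error: crude / MH 16 / MH 32 | Power at RR 0.5: crude / MH 16 / MH 32 |
| --- | --- | --- |
| Weak | 5.0% / 5.1% / 5.1% | 84.9% / 84.5% / 82.1% |
| Moderate | 4.4% / 4.6% / 5.1% | 84.3% / 84.9% / 82.6% |
| Strong | 3.8% / 5.2% / 4.8% | 84.6% / 86.5% / 84.9% |

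Simulation error is about 0.3 points for type I error and 0.7 for power. Accounting for the 16 strata changes power by −0.4, +0.6 and +1.9 points.

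A second simulation (3,000 trials, 25% vs 12.5%, odds ratios 1.5–2.5) adjusted for the four factors and baseline ventilation. Power was 80.2% crude and 81.9% adjusted (+1.7 points); type I error was 4.8% and 5.4%.

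Full cross-stratification is not the way to do it: 300/16 = about 19 patients per stratum, but 300/32 = about 9, and power over 32 cells was below crude in two of the three scenarios.

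**4. Chance imbalance in baseline ventilation.** With prevalence v and 150 per arm, SD = √(2·v·(1−v)/150).

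| Assumed v | SD (points) | 10 points / SD | Chance of a gap above 10 points |
| --- | --- | --- | --- |
| 20% | 4.6 | 2.17 | about 3% |
| 30% | 5.3 | 1.89 | about 6% |
| 50% | 5.8 | 1.73 | about 8% |

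If the two baseline groups differed in risk by 15 points (assumed), a 10-point imbalance would move the risk difference by 0.10 × 0.15 = 1.5 points, against a target of 12.5. The 95% half-width for the risk difference is 1.96 × √(0.296875/150) = 1.96 × 4.45 = 8.7 points, so a shift of that size lies well inside the stated uncertainty.

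**The case against.** The strongest objection is that section 4.2 states effect measures, not models. An RR and an HR are also what an adjusted analysis reports, and covariates are commonly fixed in a statistical analysis plan, which was not available here. A reader might infer that the protocol prescribes unadjusted comparisons; the text does not support that, and its silence is not a finding. This stands in full.

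A reader might also infer that baseline respiratory support is ignored. It is not: the endpoint is conditioned on it. Leaving it out of the stratification is a design choice, and a fifth factor would make the strata sparse. That it strongly predicts the outcome is plausible but not shown. Patients already on non-invasive ventilation may be sicker, but fewer ventilation steps count as events for them, so even the direction of the risk gap is open. Chance imbalance on it is random error that the confidence interval covers, not bias.

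On the co-morbidity levels, the objection is that this is a slip for 2 or more. That is likely, since the protocol is loose with such signs elsewhere: the SIC table in Appendix 3 scores SOFA as 0, 1 and more than 2, and the SIC threshold is above 4 in section 2.2.1 but at least 4 in section 1.1.3. A likely slip in an allocation rule still has to be corrected. What does not follow is that patients were refused or misallocated. The protocol does not show how the system codes the factor, and inconsistent coding before a concealed allocation would weaken balance without biasing the comparison.

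**Conclusion.** The co-morbidity gap in section 3.1 holds as a matter of logic and rests on no assumption. It is a stated error in an operative rule, with limited consequence: uncertain stratum assignment for one group of patients and weaker balance on one factor.

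The covariate point holds only as an improvement. Its expected gain is about 0 to 2 points of power, and that rests on assumed odds ratios, ventilation prevalence and control risk. A crude analysis would be valid, with type I error from nominal (5.0%) to slightly conservative (3.8%). No wrong conclusion follows from it, and the sample size of 300 is unaffected.

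**What to change.** 1. In section 3.1, restate the co-morbidity levels as 0–1 and 2 or more, and check the cut-off programmed in the web system. If the system already places two co-morbidities in the upper level, only the text changes. If patients have already been randomised under another coding, document how those with two were classified.

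2. Preferably, add to section 4.2 (or confirm in the statistical analysis plan) that the primary RR is adjusted for the four stratification factors and for respiratory support at randomisation (standard oxygen or non-invasive ventilation), as main effects. Use modified Poisson regression with robust errors or standardised logistic regression. Use a Cox model with the same covariates for the HR, and report the crude RR as supportive.

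The cost is one cut-off and a few sentences. The stratification variables are needed to randomise, and the endpoint already requires baseline support to be known, so no new data are needed. The downside is a little more modelling, and the adjusted HR is a conditional measure that need not equal the crude one.
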